## **Trial registration**

This trial has been registered at Chinese Clinical Trial Registry, with approval number ChiCTR2200058123.

## **Protocol version**

Version number: 3.0. Version data: February 20, 2022

## **Funding**

This study was supported by National Natural Science Foundation of China (82174527); the special project of “Lingnan Modernization of Traditional Chinese Medicine” within the 2019 Guangdong Provincial Research and Development

Program (2020B1111100008); the Innovation Team and Talents Cultivation Program of the National Administration of Traditional Chinese Medicine (ZYYCXTD-C-202004); and the Project of First Class Universities and High-level Dual Discipline for Guangzhou University of Chinese Medicine.

## **2. Introduction**

### **2.1 Background**

#### **2.1.1 The situation of opiate abuse remains grave**

Opioid Use Disorder (OUD) represents an addictive condition characterized by intense cravings for opiate substances, increased tolerance, difficulty in reducing usage, and notable withdrawal symptoms upon cessation [1,2]. Opioid substances encompass both natural and synthetic compounds. The former includes poppy, opium, morphine, and heroin, while the latter mainly consists of methadone, pentazocine, buprenorphine, and other medically synthesized opioid analgesics like fentanyl [3]. Both domestic and international scenarios regarding opiate substance abuse face daunting challenges. According to the "World Drug Report 2021" [4], as of 2020, approximately 275 million individuals globally were drug users, with opiate drugs still contributing the most to the disease burden caused by illicit substances. Moreover, over the past decade, the global usage of opioid drugs has nearly doubled. In 2019 alone, drug abuse resulted in almost 500,000 deaths worldwide, with 70% attributed to the misuse of opioid drugs. By the end of 2020, around 1.8 million people were using illicit drugs in China, with 734,000 opiate users accounting for 40.8% of the total drug users [5]. Opioid dependence poses significant threats and risks to public health and safety.

#### **2.1.2. A large population undergoing methadone maintenance treatment (MMT) has a demand for methadone dose reduction**

Methadone, an artificially synthesized opioid medication, is the cornerstone of

methadone maintenance treatment, a community-based substitution therapy for opioid substances. MMT uses legal methadone to replace of illegal opioid to treat opioid substance dependence [6,7]. It is the main intervention for the treatment of OUD worldwide [8,9]. The effectiveness of MMT in treating OUD is unquestionable, but associated issues have become increasingly apparent. As a synthetic opioid medication, methadone carries addictive potential and the risk of misuse [10]. Its toxicity exposes patients to a heightened risk of QT prolongation and arrhythmias, even at lower doses [11,12]. As the duration of treatment progresses, tolerance to methadone also increases, necessitating higher doses to maintain therapeutic effects, thereby raising the risk of overdose-related fatalities [13]. Moreover, reports indicate a persistent rise in constipation among MMT clients [14], with insomnia detection rates ranging from 58.2% to 85.8% [15]. Patients experience varying degrees of anxiety, depression, and other symptoms for a considerable period [16], while MMT-related sexual dysfunction is also prevalent [17-19]. Furthermore, the longer the duration of methadone treatment, the higher the likelihood of heroin misuse behavior [20].

MMT clients have a need to reduce the methadone dose, but the effectiveness of reducing the methadone dose by themselves is limited [21,22]. Due to the impact of side effects and aspirations for complete recovery, patients gradually reduce their doses to achieve complete cessation of medication and detoxification. Studies have shown that 40% to 57% of patients undergo the dose reduction process [22-26], and following adequate maintenance treatment, patients can gradually taper off with lower doses and attempt medication cessation [27]. Therefore, MMT clients necessitate effective and safe treatment methods to achieve methadone dose reduction, alleviate methadone toxicity, and concurrently reduce relapse behavior triggered by drug cravings.

### **2.1.3 Acupuncture has the potential to ameliorate withdrawal symptoms and alleviate drug cravings associated with opioid medications. There is still a lack of robust evidence in this field.**

Acupuncture, as an integral component of traditional Chinese medicine, boasts a

history spanning thousands of years in disease treatment. It is characterized by its simplicity of practice and remarkable therapeutic efficacy, which has led to its endorsement by the World Health Organization (WHO) for treating over 40 different conditions [28]. Also, acupuncture has been recognized by the WHO as a non-pharmacological therapy for treating drug dependence, with the potential to reduce relapse by inhibiting attentional bias towards heroin, mitigating complications associated with drug dependence and facilitating opiate withdrawal syndrome [29-32].

Several studies have identified the potential role of acupuncture in improving opioid dependence by reducing opioid use and diminishing craving. [33-35]. In a randomized controlled trial (RCT) conducted by Chan et al. [36] indicated that compared to the sham group, the real four-week-acupuncture group exhibited a significant reduction in daily methadone consumption and a notable improvement in sleep latency. In a pilot RCT by Deng et al. [37], acupuncture was found to assist in reducing medication dosages among patients already using opioids and alleviate opioid cravings among individuals not currently on opioid medication. Another study by Crawford et al. [38] discovered a 45% reduction in the overall prescription of opioids among 172 patients who had undergone acupuncture treatment at a United States Air Force medical center at least four times. Baker et al. [39] conducted a systematic review suggesting that auricular acupuncture may be an effective adjunctive therapy, improving methadone retention rates and reducing the maintenance dose.

Our group has previously conducted a clinical trial and literature review to initially explore the potential of acupuncture in reducing the daily consumption of methadone and opioid cravings in MMT clients. Our RCT demonstrated that acupuncture surpasses standalone methadone therapy in reducing methadone dosage, improving drug cravings, and addressing insomnia without concomitantly increasing the rate of positive urine tests for opioids [40]. Meanwhile we also assessed the economic value of acupuncture from a health economics perspective in this trial [41]. Another study conducted a comprehensive and systematic evaluation of acupuncture and non-pharmacological therapies for improving drug dependence and addressing

neurological symptoms, revealing the potential of acupuncture to alleviate withdrawal symptoms and enhance neurological function among individuals with substance dependence [42,43].

In general, although there have been several studies focusing on acupuncture as an adjunct treatment for drug addiction, they have predominantly consisted of small-sample clinical trials without the inclusion of sham acupuncture as a control. Consequently, there is a compelling need to undertake high-quality prospective RCT incorporating sham acupuncture as a control in order to substantiate and affirm the efficacy and safety of acupuncture in MMT, thereby providing more persuasive evidence.

#### **2.1.4 Summary**

As of the end of 2019, there were 764 community MMT clinics treating approximately 112,000 individuals in China [7]. The large scale of the MMT population has significantly increased healthcare costs and consumed social workforce and welfare resources, imposing a heavy burden on patients, their families, healthcare providers and society. The intervention efforts targeting the MMT population hold great importance in promoting public health and well-being in our country. Therefore, based on previous studies, this study establishes a placebo acupuncture group as a control and executes a more comprehensive and rigorous RCT to further validate the efficacy of acupuncture in reducing methadone dose and preventing relapse among MMT clients. The objective is to provide effective treatment strategies as a reference for MMT clients to reduce their methadone reliance and alleviate the burdensome side effects while offering high-quality clinical evidence for the use of acupuncture for MMT clients.

#### **2.2 Study Objectives and Hypothesis**

The aim of this study is to evaluate the efficacy and safety of manual acupuncture intervention for MMT clients through a multicenter clinical randomized controlled trial, comparing it with non-penetrating sham acupuncture.

### **3 Study Design and Methods**

#### **3.1 Study Design**

This is a parallel-arm, patient-blinded, multicenter, randomized, controlled trial. All eligible individuals will be randomly assigned to the manual acupuncture group or the sham control group through central randomization in a 1: 1 ratio. The time period of this trial consists of one week of baseline assessment, 8 weeks treatment period following randomization and a follow-up period of an additional 12 weeks post-treatment. The study flowchart of study procedure is presented in **Figure 1**.

#### **3.2 Randomization, Allocation, and Blinding**

Eligible patients are randomly assigned in an equal ratio to the manual acupuncture group or the sham control group via a central randomization system designed by the Clinical Research and Big Data Laboratory, South China Research Center for Acupuncture and Moxibustion, Guangzhou University of Chinese Medicine (<http://47.119.117.255/>). The randomization sequence is generated in the block size of 4. Participants will be informed that they have an equal chance to be assigned to the manual acupuncture group or the sham control group. After participants sign the informed consent form and complete baseline assessments, the researcher applies for the randomization number and allocates participants to each group. Allocation of participants is performed by an independent researcher at the clinical site who is not involved in the outcome assessment. Due to the nature of this study, acupuncturists are not blinded to group allocation. However, the outcome assessors, physicians who prescribe patient's methadone, national government personnel who is responsible for recording daily consumption of methadone, data collectors, and statisticians are all blinded to group allocations. Besides, an independent researcher supervises the conversation between acupuncturists and physicians to avoid them communicating issues related to the allocation. Upon the culmination of 8 weeks intervention, patients will be asked to guess whether they perceived the insertion of the needle tip into their skin to assess the efficacy of blinding maintenance.

[figure not shown]

Figure 1: Flowchart of trial procedures

\*A: Daily Consumption of Methadone; B: Visual Analog Scale (VAS) for opioid craving;  
C: Clinical Opioid Withdrawal Scale (COWS); D: Beck Anxiety Inventory (BAI); E: Beck Depression Inventory II (BDI-II); F: Pittsburgh sleep quality index (PSQI)

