## **Appendix 2: General principles for dosing determination of methadone maintenance treatment**

Methadone dosing in methadone maintenance treatment should be individually assessed and administered by the clinic physician based on the characteristics of the patient, taking into account factors such as the patient's physical condition, severity of drug dependence, and treatment outcome. All doses are dispensed under the direct observation of the clinic nurse and no doses are taken home.

Here are the general principles of methadone dosing in methadone maintenance treatment:

**Initial Dose:** The initial dose of methadone should be adequate to block cravings for other opioids and alleviate withdrawal symptoms. The starting dose typically ranges from 30 to 40 milligrams per day, depending on individual patient characteristics.

**Dose Adjustment:** After the initial dose, the methadone dose should be gradually adjusted based on the patient's response and needs. In general, the methadone dose is increased by 10 mg every 2 days, and as long as there are no complaints of sedation or side effects, the target dose is 60-120 mg per day.

**Dose Stability:** Once the patient's dose reaches a stable level that effectively controls withdrawal symptoms and cravings, clinic physician should maintain that dose while monitoring treatment efficacy and safety.

**Dose reduction:** methadone dose reduction should be provided when patient on dose stability stage requests a dose reduction. The rate of reduction is generally no more than 5% every two weeks. The clinic physician should closely monitor the patient's response. If adverse reactions occur, stop the methadone dose reduction process and, if necessary, return the methadone dose to the pre-tapering level.

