### **7.4 Analyses for Outcomes**

The analysis of proportion of participants with at least 20% reduction from baseline in the amount of methadone dose is performed using a generalized linear mixed model. For opioid craving VAS and all secondary outcomes, analysis is conducted utilizing a

linear mixed-model. For above models, values measured at baseline are used as covariates; intervention assignment, visit and intervention  $\times$  visit interaction are as fixed effects; and treatment centre and centre  $\times$  intervention interaction are as random effects. Before building the final model, we assess the poolability of treatment effects across centres by including centre  $\times$  intervention interaction in the model. If *P*-values corresponding to the interaction term for both primary endpoints are greater than 0.10, the treatment effect is homogenous across centres and centre  $\times$  intervention interaction will not be included in the final model. Primary outcomes use 2-sided tests at the 2.5% significance level. All other statistical tests are 2-sided at the 5% significance level. Dynamic data on the reduction in the methadone consumption and the opioid craving VAS score will be demonstrated in the figures, separated by two groups. Each row in the figures represents the reduction dose of the daily consumption of methadone (the opioid craving VAS score) for one participant. To investigate the relationship between daily consumption of methadone and the intensity of opioid craving over a 20-week period, scatter plots will be employed as a visual representation in this study with the x-axis representing the opioid craving VAS and the y-axis representing the methadone dose. The resulting scatter plot allows for the examination of the correlation between these two variables, providing insights into the potential influence of methadone intake on opioid craving levels over time.

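### Section 3.2 fixes one block size of 4 and does not say whether the list is per centre or trial-wide: the first makes allocations partly predictable, the second leaves centre balance to chance

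*Combined protocol and SAP*

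**What the plan says.** Protocol section 3.1 describes a "patient-blinded, multicenter, randomized, controlled trial" with assignment "through central randomization in a 1: 1 ratio". Section 3.2 adds that this is done "via a central randomization system designed by the Clinical Research and Big Data Laboratory", and then: "The randomization sequence is generated in the block size of 4". No other block size, random variation in block size or stratification factor is mentioned. The SAP has no section on randomisation.

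On who does what, section 3.2 says: "After participants sign the informed consent form and complete baseline assessments, the researcher applies for the randomization number and allocates participants to each group". The allocator is an on-site researcher described as independent of outcome assessment; nothing is said about independence from screening or recruitment. The same section states that "acupuncturists are not blinded to group allocation". Prescribers, dose recorders, outcome assessors, data collectors and statisticians are blinded, and talk between acupuncturists and physicians is supervised. Section 13 gives acupuncturists a brochure about the protocol, without saying what it contains.

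Centre enters the plan at the analysis stage. Protocol section 11 and SAP 7.4 include centre and centre × intervention as random effects, and SAP 7.4 states that "we assess the poolability of treatment effects across centres". Appendix 2 says that methadone dosing "should be individually assessed and administered by the clinic physician".

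**The concern.** Central randomisation after consent hides the list, but it does not stop someone inferring the next assignment from past ones. With a small fixed block, that inference can be exact. Whether and when to approach a patient is decided before consent. The entry criterion that a patient wants to taper leaves room for judgement, and motivation to taper plausibly affects the first primary outcome, a dose reduction of at least 20%. If assignments could be foreseen, the arms could differ in motivation from the start.

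That risk depends on the lists being per centre. With one trial-wide list, a site sees only scattered members of each block and can infer little. The arms are then not balanced within a centre by design. Since the clinic physician sets the dose individually, tapering practice may differ between centres, and chance imbalance would mix centre practice with treatment. The text fits either arrangement, so a reader cannot tell which cost applies.

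**Working it through.** The documents give no figure for predictability or centre balance, so there is none to reproduce.

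**Inputs.** Block size 4 (section 3.2); ratio 1:1 (section 3.1); planned total 100 (section 10). The number of centres is not in the available text. I assume 5 equal centres of 20 for the main illustration and 2 to 10 centres for the range.

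**Case A: a separate block-of-4 list per centre.** The observer knows the block size and every earlier allocation at the centre, and guesses the arm with more places left.

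- Position 1: both arms have 2 places left; P(correct) = 1/2.
- Position 2: 2 of the 3 remaining places belong to the other arm; P(correct) = 2/3.
- Position 3: the first two match with probability 1/3, which makes the third certain; otherwise it is a coin toss. P(correct) = 1/3 × 1 + 2/3 × 1/2 = 2/3.
- Position 4: always certain; P(correct) = 1.

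Best-guess accuracy = (1/2 + 2/3 + 2/3 + 1)/4 = 2.833/4 = **70.8%**, against 50% by chance.
Allocations certain in advance = (1/3 + 1)/4 = **33.3%**.
The arm difference within a centre never exceeds 2.

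**Case B: one trial-wide block-of-4 list.** In 3,000 simulated trials of 100 patients per setting, an observer who sees only their own centre guesses right 53% of the time with 2 centres and 51% with 10. Prediction is close to chance.

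Probability that a given centre of 20 is split 13:7 or worse:

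- Binomial(20, 0.5): 2 × P(X ≥ 13) = 0.263.
- Hypergeometric (20 drawn from 100, of whom 50 are in each arm): 2 × P(X ≥ 13) = 0.211.

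The range is therefore **about 21% to 26%**.

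| Centres | Mean arm difference per centre | Mean of largest difference | 95th percentile of largest |
|---|---|---|---|
| 2 | 4.0 | 4.0 | 10 |
| 3 | 3.7 | 5.6 | 11 |
| 5 | 3.2 | 6.0 | 10 |
| 10 | 2.4 | 5.6 | 8 |

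The precision cost of a 13:7 split follows from variance proportional to 1/n₁ + 1/n₂. That is 1/13 + 1/7 = 0.220, against 1/10 + 1/10 = 0.200 for 10:10. Relative efficiency is 0.200/0.220 = 91%. For 7:3 in a centre of 10 it is (1/5 + 1/5)/(1/7 + 1/3) = 0.400/0.476 = 84%.

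**Effect of varying the block size.** I simulated per-centre lists for an observer who knows the possible sizes but not their order, over 20 and over 100 patients per list.

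| Block sizes | Certain in advance | Best guess correct |
|---|---|---|
| 4 only | 33% | 70.8% |
| 4 and 6 | about 5% to 6% | about 69% |
| 4, 6 and 8 | about 2% | about 67% to 68% |

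Varying the size removes most of the certainty but little of the guessing advantage. The guessing advantage disappears only if the observer does not know earlier allocations.

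**The case against.** Four points can be made for the plan.

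First, a reader might infer that randomisation is not stratified by centre. The documents do not support that: section 3.2 neither states nor excludes it.

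Second, a reader might infer that the block size was public and that site staff knew every past allocation. That is not documented either. The block size is in the protocol, but nothing says recruiters were told it. Acupuncturists are unblinded, which need not mean that each knows the whole centre's history, and they are not said to recruit, screen or allocate.

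Third, there are real protections: a central system, the number requested only after consent and baseline, a baseline week before allocation, blinded prescribers and assessors, and supervised contact between acupuncturists and physicians. Selecting patients would require predicting, about a week ahead, who will be next in the queue.

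Fourth, under a trial-wide list the imbalance is chance rather than bias, centre is in both models, and a 13:7 split keeps 91% efficiency.

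All four stand as limits on the claim. They do not close the gap: the on-site allocator necessarily sees allocations and is not stated to be separate from recruitment, and the supervised conversations do not cover recruiting staff. A fixed block of 4 is also a stated rule, not merely an omitted detail.

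**Conclusion.** The point holds as a conditional weakness that is cheap to remove. It is not a demonstrated failure of concealment. The two costs are alternatives and must not be added together.

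Per-centre lists would leave one third of allocations certain and 70.8% guessable to someone who influences enrolment and knows both the block size and that centre's history. A trial-wide list would leave prediction near chance, with a 21% to 26% probability of 13:7 or worse in a given centre. That second figure rests on the assumption of 5 centres of 20. The consequence in that case is mainly lost precision and weaker comparability between arms within centres. It is not systematic bias, and at a 13:7 split the effect on the poolability check is modest.

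**What to change.** In protocol section 3.2, replace the block-size sentence with a statement that:

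- the central system uses a separate permuted-block list for each centre, with block sizes varied at random (for example 4 and 6, or 4, 6 and 8);
- block sizes are held only by the randomisation laboratory and kept out of site documents and the acupuncturist brochure;
- staff who screen and recruit are not given earlier allocations.

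The third item matters most, for the reason shown in the second table. The SAP models already contain centre and need no change.

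The cost is a small amendment to an ethics-approved protocol and a system setting. If made during enrolment, it leaves two schemes in one trial. Incomplete blocks allow slightly larger imbalance: the within-centre cap rises from 2 under per-centre blocks of 4 to 3 with sizes 4 and 6, or 4 with 4, 6 and 8. If the current list is trial-wide, the change also trades some added predictability within a centre (from 51% to 53% up to about 67% to 69% for an observer who knows the history) for centre balance.

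If enrolment is complete, report which kind of list was used and tabulate arm by centre.

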#### 4. Eligibility Criteria

##### 4.1 Inclusion Criteria

Patients will be included if they have:

- Diagnosed as opioid dependence according to the fifth edition of the Diagnostic and Statistical Manual of Mental Disorders (DSM-5) (Appendix 1) [44];
- Aged between 18-65 years;
- Received MMT for more than 6 weeks;
- Demand for methadone tapering;
- Not having received any kind of acupuncture therapy during the previous 3 months.

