## **4.2 Exclusion Criteria**

Patients will be excluded if they have:

- Serious heart, liver, lung, or kidney diseases;
- Syphilis or AIDS;
- Severe digestive disease or malnutrition;
- Severe primary hematological disorders;
- Received other treatment that may affect the efficacy evaluation of the present intervention;
- Infection, inflammation, scar, or injury close to the site of the selected acupoints;
- Pregnancy, or plans for pregnancy;
- Had a history of mental illness other than drug dependence.

In addition, all patients are instructed not to take any other medications aiming at alleviating withdrawal symptoms, improving sleep quality, or managing depression and anxiety during the study, in order to avoid initiating other interventions. Patients who consume such medications are excluded from the study.

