## **6. Outcome**

### **6.1 Primary Outcomes**

#### **6.1.1 The Rate of Methadone Dose Reduction**

One primary outcome is the rate of methadone dose reduction, defined as the proportion of participants who achieve a reduction in methadone dose of  $\geq 20\%$  compared to baseline after 8 weeks of intervention. Based on the results of previous studies and the standards and clinical guidelines of MMT in the United States and Canada, we find that achieving a reduction in methadone dose of  $\geq 20\%$  at the end of intervention is associated with significant clinical benefits[40,41,48,49]. Therefore, a 20% reduction in methadone dose is used as the threshold to define significant improvement in tapering effectiveness.

Enrolled patients come to visit the clinic every day to take methadone, which is strictly administered by the physicians as required by the MMT clinics. Daily consumption of methadone from baseline to the 20th week will be obtained from physicians and recorded by independent research assistants, which is used to calculate average daily methadone dose per week and the rate of methadone dose reduction.

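### Entry does not ask whether the methadone dose was stable or already falling, and the dose model ignores the pre-randomisation trend; this costs precision and clarity but does not bias the comparison

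*Combined protocol and SAP*

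**What the plan says.** Protocol 4.1, repeated in SAP 3.2.1, lists two entry conditions that bear on dose history: "Received MMT for more than 6 weeks" and "Demand for methadone tapering". Neither concerns the course of the dose before entry. The nearest exclusion, in protocol 4.2 and SAP 3.2.2, is "Received other treatment that may affect the efficacy evaluation of the present intervention". It is general and names neither a current taper nor an unstable dose.

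The trial "consists of one week of baseline assessment, 8 weeks treatment period following randomization" and then a 12-week follow-up (protocol 3.1). The responder outcome in protocol 6.1.1 is "defined as the proportion of participants who achieve a reduction in methadone dose of" 20% or more from baseline after 8 weeks. Randomisation is in blocks of 4, with no stratification by taper status described (protocol 3.2). The mixed models in protocol 11 and SAP 7.4 use the baseline value as the covariate and contain no term for dose trend.

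Appendix 2 describes clinic practice: "methadone dose reduction should be provided when patient on dose stability stage requests a dose reduction", generally at no more than 5% every two weeks. It is a general dosing principle, not an entry criterion. Section 10 assumes response rates of 70% and 36%, with 42 per group for 90% power at 5%, and 50 per group after about 15% attrition.

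**The concern.** A one-week baseline gives the level of the dose but cannot show whether it is flat, falling or recently raised. Under the stated criteria all three kinds of patient can be enrolled, and they have different chances of a 20% fall over the next 8 weeks whichever needle they receive. To the extent that a patient's dose course was set before randomisation, that patient says little about whether acupuncture enables a reduction. If there are many such patients, the arm difference shrinks, the sham responder rate becomes harder to interpret, and an uneven split by chance adds noise that the model cannot remove. The pre-entry doses were dispensed at the clinic under direct observation (Appendix 2), so the missing information should already be on record.

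**Working it through.** **1. The plan's own figure.** Inputs from section 10: p1 = 0.70, p2 = 0.36, n = 42 per group, two-sided 5% assumed for this endpoint. The pooled mean is 0.53.

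Power = Φ{[Δ√n − z√(2p̄(1−p̄))] / √[p1(1−p1) + p2(1−p2)]}
= Φ{[0.34 × 6.481 − 1.960 × 0.7058] / 0.6636} = Φ(1.236) = 89.2%.

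For 90% power the pooled formula gives 44 per group and the unpooled formula 41, so 42 is reproduced closely. 42/0.85 = 49.4, hence 50 per group.

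**2. Can a pre-existing taper alone reach the cut-off?** At the Appendix 2 pace, four steps fit into 8 weeks.

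- From a stable dose: 1 − 0.95⁴ = 18.5% if compounded, or 4 × 5% = 20.0% if linear.
- If steps are 5% of the pre-taper dose and one or two were taken before baseline: 20/95 = 21.1% or 20/90 = 22.2%.
- The same, with only three steps complete by week 8: 15/95 = 15.8% or 15/90 = 16.7%.

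An earlier taper can therefore produce a responder, but only near the margin.

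**3. Dilution.** Let a fraction f of each arm respond at rate r whatever the allocation, the rest following 70% v 36%. Neither f nor r is in the documents; f = 10% to 30% is an assumption. The difference is (1−f) × 34 points, whatever r is. With r = 70%, the acupuncture rate stays at 70% and the sham rate is 0.70f + 0.36(1−f).

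| f | Sham rate | Difference (points) | Power, 42 per group, 5% | Power, 42 per group, 2.5% |
|---|---|---|---|---|
| 0 | 36.0% | 34.0 | 89.2% | 82.5% |
| 10% | 39.4% | 30.6 | 81.6% | 72.7% |
| 20% | 42.8% | 27.2 | 71.8% | 61.1% |
| 30% | 46.2% | 23.8 | 60.2% | 48.7% |

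The last column is shown because the primary tests are run at 2.5% (protocol 11, SAP 7.4). Changing r from 36% to 100% moves power at 5% only between 81.3% and 82.2% (f = 10%), 71.0% and 73.9% (20%), and 59.1% and 64.6% (30%).

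**4. The assumptions that drive the loss.**

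- *No acupuncture effect in these patients.* Give them half the usual effect (70% v 53%). At f = 20% the sham rate is 0.2 × 53% + 0.8 × 36% = 39.4%, the difference is 30.6 points and power at 5% is 81.6%, not 71.8%. With the full effect there is no dilution.
- *The 36% excludes them.* If the planned 70% and 36% already include such patients, power stays at 89.2%.

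**5. Chance imbalance.** With f = 20% and 50 per arm, the SD of the difference in taper share is √(2 × 0.2 × 0.8/50) = 0.08. The arms then differ by 10 points or more with probability 2[1 − Φ(0.10/0.08)] = 21%. If the shares were 25% (acupuncture) and 15% (sham) with r = 70%, the sham rate would be 0.15 × 70% + 0.85 × 36% = 41.1% instead of 42.8%, a shift of 1.7 points in the arm difference. With r = 100% the rates would be 77.5% v 45.6%, a difference of 31.9 instead of 27.2 points, a shift of 4.7.

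**The case against.** Much of the opposing case stands. Enrolling anyone on MMT who wants to taper is a legitimate target population. Randomisation balances prior dose trend in expectation, and the prescribing physicians are blinded (protocol 3.2), so a pre-existing taper has no reason to run differently by arm. Section 2.1.2 says that patients' own attempts to reduce have limited success, so people part-way through a taper may be among those whom acupuncture could help. Initial upward titration is largely over by entry: on Appendix 2 figures, moving from 30 to 120 mg in 10 mg steps every 2 days takes 9 × 2 = 18 days, which leaves only later re-titration, of unknown frequency.

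Three stronger readings are tempting and are not supported:

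- A reader might infer that patients already tapering count as responders automatically. They do not: reduction before baseline earns nothing, and a further 20% is needed, which the Appendix 2 pace reaches only marginally.
- A reader might take "Studies have shown that 40% to 57% of patients undergo the dose reduction process" as the share who are mid-taper at enrolment. That figure has no time frame and does not estimate f.
- A reader might take the power losses above as the trial's actual power. They hold only under the two assumptions in step 4, which the documents neither confirm nor rule out.

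What the objection does not answer is that a prognostic feature closely tied to the primary outcome, and probably already on record, is neither collected for the trial nor used in the analysis.

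**Conclusion.** The gap is real and its consequence moderate. The eligibility criteria leave pre-entry dose course open, and the dose model cannot separate a falling, flat or recently raised dose. This is a loss of precision and interpretability, with some exposure to chance imbalance; it gives no ground for claiming directional bias. Its size cannot be settled from the documents. It ranges from no loss of planned power, if the 36% sham rate already includes such patients or acupuncture works equally well in them, to power of about 82% to 60% at 42 per group and 5%, if 10% to 30% of entrants respond equally in both arms and come on top of the 36%. A reader might also infer that entry must be restricted to stable doses. The documents do not compel that: it would change the target population and would come close to setting a clinical rule.

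**What to change.** Keep eligibility as it is and make these changes:

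1. Extract each participant's prescribed daily doses from the MMT clinic's dispensing record for a fixed window before randomisation, for example 4 weeks. The entry condition of more than 6 weeks on MMT means that this history exists for everyone.
2. In SAP 7.4, add percentage dose change over that window as a baseline covariate in the generalized linear mixed model for the responder outcome.
3. In SAP 7.5, add a sensitivity analysis of the responder outcome by taper status at entry (stable or changing), with the definition fixed before unblinding.
4. In protocol section 10, state whether the 36% sham rate includes patients already tapering.
5. Reconcile the entry criteria with the dose-stability wording in Appendix 2. How that is resolved clinically is for the sponsor; no dose-hold rule is proposed here.

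The cost is one record extraction per patient and one more model term. The gain in precision depends on how strongly prior trend predicts response, which the documents do not show.
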